### Recruitment and invitation of participants

Participants will be approached and assessed for eligibility on completion of PR by members of the clinical PR services. Interested participants will receive a participant information sheet and given at least 48 hours to consider their participation. After consultation with our patient and public involvement (PPI) group, we propose not to set a threshold for improvement in PR outcomes for patients to be considered for the trial. Those interested will receive an invitation letter to attend a consent research visit.

### Randomisation and blinding

Eligible participants will be consented and randomised using a concealed allocation web-based programme (https://www.sealedenvelope.com/). Randomisation will be 1:1 to either usual care (control) or the SPACE FOR COPD maintenance programme (intervention). Randomisation codes will be blocked per site, providing even numbers of control and intervention patients at each site and a sufficient number of participants for the intervention group sessions to run. Due to the nature of the intervention, the participants and intervention facilitators will not be blinded to group allocation. However, the assessors will be blinded to group allocation. Other blinded assessors are in place in case of blinding exposure by first blinded assessor. Any unintentional unblinding will be documented.

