## Methods and analysis

### Trial design and setting

The trial will be a prospective, multicentre, randomised controlled, single blind trial of SPACE FOR COPD maintenance programme vs usual care. There will be an integrated economic evaluation and also an embedded qualitative component. The trial will be conducted at two centres, the University Hospitals of Leicester (UHL) National Health Service (NHS) Trust in Leicester, UK, and Harefield Pulmonary Rehabilitation Unit, Harefield, UK. We have used the SPIRIT-2013 checklist and recommendations as a guide for designing this trial.^19^

The trial will consist of three visits (baseline, 6 and 12 months). Each visit will last for up to 2 hours where all outcomes will be collected. In addition, a 2-hour small group session will be conducted at month 1 after baseline visit then at months 4, 7 and 10 in the intervention group only (see figure 1). The trial recruitment will take place over 1 year, with a 1-year follow-up.

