### Data analysis

#### Quantitative analysis

All data will be analysed on an intention-to-treat basis using SPSS software (V.26.0, IBM). We will conduct a separate per-protocol analysis for those who complete the intervention. Continuous variables will be presented as mean (SD), categorical variables as frequencies (percentages). All data will be assessed for outliers, normality and analysed using appropriate parametric and non-parametric statistics. To test the primary outcome, the difference between the two groups for the ESWT time will be analysed at 12 months using an independent t-test (or non-parametric equivalent).

Secondary outcome measures will be analysed in the same way. We will also look at changes in all outcomes in individual participants over time (ie, pre-PR, post-PR, 6 months and 12 months) using a repeated measures analysis of variance (or non-parametric alternative). Significance will be set at p<0.05 and differences between groups will be expressed as mean (95% CIs). Analysis will take into account the baseline values and adjust for potential confounders (eg, age, disease severity). Missing data will be corrected for by multiple imputation. Interim data may be made available for abstracts but unmasking will not occur.

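### Randomisation is blocked by site, but the named primary test cannot include site; if the sites differ, the test is mildly conservative and the interval slightly too wide

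*Protocol article*

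**What the plan says.** Under Trial design and setting, the article says: "The trial will be conducted at two centres". Under Randomisation and blinding, allocation is 1:1 and "Randomisation codes will be blocked per site, providing even numbers of control and intervention patients at each site". Site is therefore a stratification factor, and the only one the article names.

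Under Quantitative analysis, the between-arm difference in ESWT time "will be analysed at 12 months using an independent t-test (or non-parametric equivalent"). For the rest: "Secondary outcome measures will be analysed in the same way". A later sentence in the same section adds: "Analysis will take into account the baseline values and adjust for potential confounders (eg, age, disease severity"). Site is not one of the examples, and the article does not say how this adjustment relates to the t-test. No section places site in any analysis.

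**The concern.** An analysis should normally reflect the factors by which patients were randomised. Balancing the arms within each centre makes a site effect cancel out of the difference between arm means. An ordinary two-sample t-test does not know this. Its pooled variance still contains the spread between centres, so the reported standard error exceeds the true one whenever site predicts the outcome.

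Some site difference in 12-month ESWT is plausible. Each centre recruits from its own rehabilitation service, no threshold of improvement is set for entry, and referral to community exercise schemes depends on local availability. What is at stake is precision and a little power in the primary comparison and in each secondary one.

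**Working it through.** **The plan's own figures.** The article states no figure for a site effect, so there is none to reproduce. Its sample size supplies the SD (282 s), the target difference (184 s), the total (116) and the attrition (20%). With two-sided 5% and 80% power, n per arm = 2 × (1.96 + 0.8416)² × (282/184)² = 36.9, so 37 per arm, 74 in total, and 74/0.8 = 92.5, so 93. That is not 116. This is a separate question and neither supports nor weakens the present point. It only explains why the power figures below start near 88% and not at 80%.

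**Assumptions.** The site difference D in 12-month ESWT is not in the document and is assumed. Sites are of equal size, the arms stay balanced within site among those analysed, and tests are two-sided.

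**Formula.** Let s be the within-site SD and p the share of patients at one site. The true variance of the arm difference uses s². The t-test's pooled variance estimates s² + p(1 − p)D². The reported SE is therefore too large by the factor sqrt(1 + p(1 − p)(D/s)²).

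**Reading 1: 282 s is the total SD, p = 0.5.** Then s = sqrt(282² − D²/4), the SE factor is 282/s, and the actual type I error is 2 × [1 − Φ(1.96 × 282/s)].

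| Assumed D | s | 282/s | SE too large by | Actual type I error |
|---|---|---|---|---|
| 100 s | sqrt(79,524 − 2,500) = 277.5 | 1.016 | 1.6% | 4.6% |
| 150 s | sqrt(79,524 − 5,625) = 271.8 | 1.037 | 3.7% | 4.2% |
| 200 s | sqrt(79,524 − 10,000) = 263.7 | 1.070 | 7.0% | 3.6% |

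**Reading 2: 282 s is the within-site SD, p = 0.5.** The number analysed is 116 × 0.8 = 92.8, taken as 46 per arm. With site in the model, SE = 282 × sqrt(2/46) = 58.8 s, the 95% half-width is 1.96 × 58.8 = 115.3 s, and power is Φ(184/58.8 − 1.96) = 87.9%. For the unadjusted test:

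| Assumed D | Half-width | Too wide by | Power |
|---|---|---|---|
| 0 | 115.3 s | 0 | 87.9% |
| 100 s | 117.0 s | 1.6% | 87.3% |
| 141 s | 118.8 s | 3.1% | 86.6% |
| 184 s | 121.2 s | 5.2% | 85.7% |
| 282 s | 128.9 s | 11.8% | 82.6% |

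A 70:30 split between sites gives slightly smaller excesses (1.3% at 100 s, 10.0% at 282 s).

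**Simulation** (reading 2, equal sites, 92 analysed, 20,000 runs per scenario). The t-test's mean SE was 59.6 s at D = 100 s and 61.7 s at D = 184 s, against a true SE of about 59 s. Its type I error was 0.048 and 0.040. The model with site kept a mean SE of 58.6 to 58.7 s and a type I error of about 0.05 throughout.

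**The case against.** The strongest reply is that the article does not exclude site. It promises to "adjust for potential confounders (eg, age, disease severity"), that list is open, and a final covariate list is commonly left to an analysis plan that is not shown. This stands in part: nobody can say that site will be absent from every analysis. But the article itself names the primary test, and that test cannot contain site. The adjustment sentence neither names site nor says whether it replaces the t-test.

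Second, the size rests on an assumed site difference, and 200 s already exceeds the target effect of 184 s. Baseline ESWT is measured after rehabilitation at the same centre, so adjusting for it could absorb part of a lasting site difference. If it absorbed half of 200 s, with the SD unchanged, the 100 s line would apply. This stands.

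Third, the documents limit site differences: rehabilitation must meet a national standard, walking tests follow a standard operating procedure, and facilitators are trained together and observed across sites. A reader might still point to different facilitators as a source of a site difference. Facilitators see only the intervention arm, so that argues mainly for a treatment-by-site interaction, which an additive site term does not address.

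Fourth, the harm is benign. A reader might infer a biased estimate, an inflated false-positive rate, or stratification that has been wasted. None of these follows. Balance within site still protects against confounding by site, and the article's stated reasons for blocking (even numbers at each site and enough patients to run the groups) are met whatever the analysis.

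**Conclusion.** The mismatch is real and modest. The named primary test, and the secondary analyses that follow it, cannot reflect the one factor by which the article says patients are randomised. If the sites differ by 100 to 200 s in 12-month ESWT, with equal site sizes and a total SD of 282 s, the standard error is about 1.6% to 7% too large and the test is mildly conservative. The excess is less if baseline ESWT takes up part of the difference, and nil if the sites do not differ. On the second reading of the SD, the power lost for site differences up to 184 s is at most 87.9 − 85.7 = 2.2 percentage points. Leaving out site is not by itself a source of bias or of excess false positives, so the documents do not support calling the primary test invalid. The case for change is that the improvement is nearly free.

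**What to change.** State one primary analysis: a linear model of 12-month ESWT on arm, baseline ESWT and site, with the arm difference and its 95% interval taken from that model. Add that every between-arm secondary analysis includes site. If a rank test is kept as a fallback, use a form stratified by site, such as the van Elteren test.

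This would replace "using an independent t-test (or non-parametric equivalent") as the primary method and would also settle how the promised baseline adjustment relates to the primary test. The site term costs one degree of freedom. Baseline adjustment is already promised. Site is known for every patient from randomisation, so no new data are needed and the sample size need not rise.

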### Data collection and management

The REDCAP (Research Electronic Data Capture) database housed by University of Leicester will be used to create our paper case report forms (CRFs) and transfer data to the electronic version will be performed periodically. This password-protected database has the facility to set limits, flag discrepancies and provides an audit trail of when data has been entered/amended and by whom. A random check of 10% of the data will be performed by a member of the research team not involved in data entry. Once data are ready for analysis, it can be easily exported to SPSS statistical analysis software. Paper CRFs will not contain patient identifiable data and will be stored in locked filling cabinets in key coded offices. Data will be collected and stored in accordance with the 2018 UK General Data Protection Regulation.

### Data analysis

#### Quantitative analysis

All data will be analysed on an intention-to-treat basis using SPSS software (V.26.0, IBM). We will conduct a separate per-protocol analysis for those who complete the intervention. Continuous variables will be presented as mean (SD), categorical variables as frequencies (percentages). All data will be assessed for outliers, normality and analysed using appropriate parametric and non-parametric statistics. To test the primary outcome, the difference between the two groups for the ESWT time will be analysed at 12 months using an independent t-test (or non-parametric equivalent).

Secondary outcome measures will be analysed in the same way. We will also look at changes in all outcomes in individual participants over time (ie, pre-PR, post-PR, 6 months and 12 months) using a repeated measures analysis of variance (or non-parametric alternative). Significance will be set at p<0.05 and differences between groups will be expressed as mean (95% CIs). Analysis will take into account the baseline values and adjust for potential confounders (eg, age, disease severity). Missing data will be corrected for by multiple imputation. Interim data may be made available for abstracts but unmasking will not occur.

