### Primary outcome

#### Endurance capacity

The primary endpoint at 12 months is endurance capacity measured by the Endurance Shuttle Walk Test (ESWT), expressed in seconds. The ESWT is a walking field test that has been found to be safe, valid and reproducible among patients with COPD.^23^ The minimal clinically important difference (MCID) for this population is estimated to be between 174 and 279 s.^24^

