### Sample size

The power calculation (for a continuous outcome superiority trial) is based on the primary outcome measure. We require 116 patients for an 80% chance of finding a 184 s (SD: 282 s) difference in the ESWT time between groups at 12 months (at the 5% level). The 184 s was the between group difference reported in the original primary care SPACE FOR COPD study^14^ and is similar to the suggested MCID range for this outcome (174–279 s).^24^ This number includes expected attrition of 20%.

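### The primary ESWT test is left to be chosen between a t-test and a rank test after the data are seen, and the rank option does not test the mean difference that is powered and reported

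*Protocol article*

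**What the plan says.** All references are to the protocol article.

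- **Endpoint** (Primary outcome, Endurance capacity): "The primary endpoint at 12 months is endurance capacity measured by the Endurance Shuttle Walk Test (ESWT), expressed in seconds". The section gives an MCID range of 174–279 s.
- **Powering** (Sample size): "We require 116 patients for an 80% chance of finding a 184 s (SD: 282 s) difference in the ESWT time between groups". The target is a difference with an SD, that is, a difference in means, and it is justified against the MCID range in seconds. It refers to the 12-month value and a significance level of 5%.
- **Choice of method** (Quantitative analysis): "All data will be assessed for outliers, normality and analysed using appropriate parametric and non-parametric statistics". The following sentence names an independent t-test for 12-month ESWT time and allows a non-parametric equivalent in its place. No criterion, threshold or default is given.
- **Reporting** (same section): "differences between groups will be expressed as mean (95% CIs"). No exception is made for a non-parametric result.
- **Adjustment** (same section): the analysis is to account for baseline values and potential confounders, with age and disease severity as examples. Missing data are to be multiply imputed.

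**The concern.** The protocol makes the primary test depend on the 12-month outcome data, while the quantity powered and reported stays a mean difference in seconds. The usual rank counterpart of an independent t-test, the Mann-Whitney test, asks whether a value from one arm tends to exceed a value from the other. That coincides with a mean comparison only under further conditions, such as a pure shift between arms of the same shape. Otherwise a significant rank p-value can stand beside a mean difference whose interval includes zero, or the reverse.

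Two things are at stake for the primary conclusion: whether the p-value and the reported effect describe the same quantity, and whether an analyst's choice made after seeing the data can decide the result. The section also promises baseline adjustment, which neither named test provides in its plain form, so neither branch is the analysis that the section goes on to describe.

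**Working it through.** **Inputs from the protocol article.** Difference 184 s, SD 282 s, power 80%, 5% level (taken as two-sided; the sidedness is not stated), 1:1 allocation, 116 recruited, 20% attrition included.

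**The plan's own figure.** Per arm, n = 2 × (1.960 + 0.842)² × (282/184)² = 36.9, so 37; the exact t-test gives 38. With 20% attrition, 74/0.8 = 92.5, so 93 (95 from the t-test). The stated 116 is not reproduced; it matches inflating twice, 74/0.8/0.8 = 115.6. That is a separate matter and errs towards more power. It matters here only because 116 × 0.8 = 92.8 leaves about 46 per arm, which gives about 87% power for 184 s by t-test. Fixing a mean-based analysis therefore does not threaten the planned 80%.

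**Would the switch occur?** Walking time cannot be negative. With SD 282 s, a normal distribution with mean below 1.96 × 282 = 553 s puts more than 2.5% of values below zero. The protocol gives no mean, so skew is plausible but not shown. It also names no normality check. If one assumes Shapiro-Wilk at 5% in each arm, with 46 per arm, the rank test is chosen in about 100% of trials with lognormal times (mean 350 s, CV 0.8, or mean 400 s, SD 282 s). With truly normal times it is chosen in about 10%, as expected from 1 − 0.95² = 9.75%.

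**Why the tests can differ.** A lognormal with mean m and coefficient of variation c has median m/√(1 + c²). With both means 350 s and c = 0.6 and 1.0, the medians are 350/√1.36 = 300 s and 350/√2 = 247 s. The mean difference is 0 s, but a value from the first arm exceeds one from the second with probability Φ((ln 300 − ln 247)/√(ln 1.36 + ln 2)) ≈ 0.58 rather than 0.50. A rank test is right to detect that, but it is not a difference in mean seconds.

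**Rejection rates with equal means** (two-sided 5%, lognormal, 46 per arm, 4,000 or more simulated trials per row):

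| Mean | Spread in the two arms | t-test | Rank test |
|---|---|---|---|
| 350 s | CV 0.8 v 0.8 | about 5% | about 5% |
| 350 s | CV 0.75 v 0.85 | about 5% | about 6% |
| 350 s | CV 0.7 v 0.9 | about 5% | about 9% |
| 350 s | CV 0.6 v 1.0 | about 6% | 23–24% |
| 400 s | SD 200 v 345 s | about 6% | about 22% |

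In the last row the two tests reach different conclusions in about 19% of trials. The simulation error, 1.96 × √(0.24 × 0.76/4000), is about 1.3 percentage points at 24%, and smaller at 5%.

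**Power when the true mean difference is 184 s** (46 per arm):

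| How the benefit is spread | t-test | Rank test |
|---|---|---|
| Uniform shift, normal times | about 87% | about 86% |
| Uniform shift, lognormal times | about 87% | about 99% |
| Proportional gain, 350 to 534 s, CV 0.8 | about 72% | about 79% |
| 30% of patients gain 613 s (0.3 × 613 = 184), control mean 400 s, SD 200 s | about 88% | about 66% |
| The same responder pattern, control mean 350 s, CV 0.8 | about 72% | about 60% |

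The direction depends on how the benefit is distributed, which nobody knows in advance.

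**The case against.** The strongest reply has four parts.

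- **Condensation.** The normality criterion, the exact rank test and the form of a non-parametric report are details that an article leaves to a full protocol or SAP. The reporting sentence is also generic, covering all outcomes. This stands for those details. It does not cover the open choice itself: the article states a data-dependent choice for the primary outcome and fixes a mean difference for powering and reporting.
- **Size.** The 23–24% figure needs equal means with markedly unequal spread, and nothing in the article suggests that pattern. This stands, and is why the range is shown. Those distributions also truly differ, so the figure measures a mismatch of target. A reader might infer that the switch inflates type I error; with identical arms it stays near 5%.
- **Power.** A reader might infer that the rank branch is underpowered. That is not generally so: it gains under a shift in skewed data and loses when the benefit sits in a subgroup.
- **Attribution.** A reader might infer that switching is what drops the baseline adjustment, that a rank analysis can give nothing in seconds, or that outliers will be removed. The documents support none of these. The plain t-test does not adjust for baseline either. A Hodges-Lehmann shift is in seconds and could be set against the MCID, although it is not a mean difference and is not mentioned. The section says only that outliers are assessed.

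**Conclusion.** The point holds in this form: the primary test is not fixed, and one of the two permitted options does not test the mean difference that the trial is powered on and says it will report. When means are equal, rank-test rejection runs from about 5% to 23–24% according to how far the arms differ in spread, against about 5–6% for the t-test. When the true mean difference is 184 s, the rank test's power ran from about 60% to 99% and the t-test's from about 72% to 88%, with neither uniformly better.

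These sizes rest on assumed ESWT distributions, since the article gives only an SD, and on 46 evaluable per arm. The switch rates also assume a Shapiro-Wilk rule that the article does not state. The mismatch between test and reported effect does not depend on those assumptions; how often it would change the conclusion does. The plan should be changed, but this is not a flaw that by itself invalidates the trial.

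**What to change.** In the primary-outcome sentence of the Quantitative analysis section, delete the parenthesis that permits a non-parametric equivalent, and replace the t-test with one named analysis to be used whatever the distribution:

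- a linear model of 12-month ESWT time on randomised group, adjusted for baseline ESWT and for site (randomisation is blocked by site);
- the adjusted mean difference in seconds as the effect, with a robust (HC3) or bootstrap 95% CI to allow for skew;
- a rank-based or log-time analysis as a named sensitivity analysis, with its own effect measure stated.

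This also removes the conflict between the named test and the promise to account for baseline, and a linear model combines readily with the planned multiple imputation.

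The cost is wording only, with no change to sample size or data collection. The downside is some loss of power if the effect is a pure shift in very skewed data (about 87% against 99% in the case above), which still exceeds the planned 80%.

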### Study outcomes

The assessments described below will be conducted at baseline, 6-month and 12-month visits and completed by a blinded assessor, unaware of the group allocation. Due to the impact of COVID-19 restrictions, assessment visits and consent may be completed over the phone for all data other than physical tests where this is not possible (ie, spirometry/walking tests). Consent form for patients shown in online supplemental file 1.

10.1136/bmjopen-2021-055513.supp1Supplementary data

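### The article does not say whether the unadjusted t-test or a baseline-adjusted comparison of 12-month ESWT is the primary analysis, and the named test gives up precision that baseline ESWT could supply

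*Protocol article*

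**What the plan says.** The article defines the endpoint under Endurance capacity: "The primary endpoint at 12 months is endurance capacity measured by the Endurance Shuttle Walk Test (ESWT), expressed in seconds". Under Quantitative analysis it names the test: ESWT time at 12 months is to be compared between the arms "using an independent t-test (or non-parametric equivalent"). The second paragraph of that section begins "Secondary outcome measures will be analysed in the same way", then describes a repeated measures ANOVA for change within participants over time, sets the significance level, and adds: "Analysis will take into account the baseline values and adjust for potential confounders (eg, age, disease severity").

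Baseline ESWT will be available, because under Study outcomes "The assessments described below will be conducted at baseline, 6-month and 12-month visits". The Sample size section plans a simple two-group comparison: "We require 116 patients for an 80% chance of finding a 184 s (SD: 282 s) difference in the ESWT time between groups at 12" (that is, at the 12-month visit). It makes no allowance for a baseline correlation.

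**The concern.** An independent t-test on 12-month values, or its rank equivalent, has no place for a baseline value, age or disease severity. If the adjustment sentence covers the primary outcome, a second and different analysis of that outcome is promised, with its own estimate and p-value. The article does not say what that model is or which of the two results decides the trial. If they fell on opposite sides of 0.05, nothing in the text would settle the conclusion. Because the secondary outcomes inherit the primary method, they inherit the same uncertainty.

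Precision is also at stake. The trial asks whether gains held at discharge from pulmonary rehabilitation are preserved, and ESWT is measured at that point. An unadjusted comparison leaves the variation between patients in discharge ESWT in the error term, and it carries any chance imbalance between arms into the estimate in proportion to the correlation.

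**Working it through.** **Inputs.** From Sample size: difference 184 s, SD 282 s, 80% power, 5% level, 116 patients including 20% attrition. From Randomisation and blinding: 1:1 allocation, blocked per site. Assumed: a two-sided test; 282 s is the SD of 12-month ESWT time; the correlation r between baseline and 12-month ESWT is 0.3 to 0.7, because the article gives none.

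**The plan's own figure.** n per arm = 2 × (1.96 + 0.842)² × 282² / 184² = 36.9, so 37 per arm and 74 in total. Dividing by 0.8 gives 93. An exact t calculation gives 38 per arm, or 95–96 after attrition. The stated 116 does not follow from its inputs, but it errs on the generous side. That is a separate matter and does not affect this point. The calculations below keep the planned 116.

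**Completers.** 116 × 0.8 = 92.8, so about 46 per arm. This treats the analysis as complete-case; the article plans multiple imputation, so 46 is an approximation.

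**Unadjusted test.** SE = 282 × √(2/46) = 58.8 s. The 95% half-width is 1.96 × 58.8 = 115 s. Power = Φ(184/58.8 − 1.96) = Φ(1.17) = 87.9%, or 87.2% by the exact noncentral t.

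**Baseline-adjusted ANCOVA.** Residual SD = 282 × √(1 − r²), so the variance falls by r².

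| r | Variance removed | Residual SD | 95% half-width | Power (normal) | Power (t, 89 df) |
|---|---|---|---|---|---|
| unadjusted | – | 282 s | 115 s | 87.9% | 87.2% |
| 0.3 | 9% | 269 s | 110 s | 90.7% | 90.1% |
| 0.5 | 25% | 244 s | 100 s | 95.1% | 94.7% |
| 0.7 | 49% | 201 s | 82 s | 99.2% | 99.1% |

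**Chance imbalance.** The article gives no baseline SD. If it is also assumed to be 282 s, one standard error of the baseline difference is 58.8 s, about 59 s. The regression slope of 12-month on baseline ESWT is then r, so such an imbalance shifts the unadjusted estimate by r × 58.8:

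- r = 0.3: 17.6 s (17.6/184 = 10% of the planned difference)
- r = 0.5: 29.4 s (16%)
- r = 0.7: 41.2 s (22%)

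**The case against.** The t-test is tied by name to the primary outcome. The adjustment sentence names no outcome and comes later, after the general statement on significance and intervals. A natural reading is an unadjusted primary test with adjusted analyses alongside it. This stands in part. A reader might infer that the two sentences cannot both be carried out. They can, as two separate analyses; what is missing is a statement of which is primary.

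A reader might also infer that the t-test is biased or leaves the trial underpowered. The article does not support that. Allocation is randomised and concealed, so the unadjusted difference is unbiased over repeated randomisations. Its power on the stated inputs exceeds the planned 80%. The primary aim is worded as a comparison at 12 months, which the t-test does answer.

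Third, the covariates appear only as examples, and one might infer a model left to be chosen after unblinding. No passage says so. A journal article commonly leaves the full covariate list to an analysis plan that is not shown here, so the open list is not counted as a fault.

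Finally, the gain rests on an assumed correlation. At r = 0.3 it is small: 5 s of half-width and about 3 percentage points of power.

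What the objection does not remove is that the article names one primary test, makes an unrestricted promise of adjustment that this test cannot meet, and does not rank the results.

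**Conclusion.** The point holds as an ambiguity with a cost in precision. Two candidate primary results exist for 12-month ESWT, one from a named unadjusted test and one from an unnamed adjusted model, and the article does not choose between them. The unadjusted test is valid and adequately powered on the document's own figures.

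The loss of precision ranges from slight (half-width 115 s against 110 s at r = 0.3) to substantial (115 s against 82 s at r = 0.7). This assumes 46 completers per arm and an SD of 282 s at 12 months. The shift of 18–41 s from a one-standard-error imbalance rests on the further assumption of the same SD at baseline. It describes what one unlucky allocation would do, not an average bias.

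This should be corrected before any comparison between groups is seen. It does not put the validity of the trial in doubt.

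**What to change.** Replace the t-test sentence under Quantitative analysis with:

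> The primary analysis is an ANCOVA (linear regression) of 12-month ESWT time on randomised arm, adjusting for baseline ESWT time and site, fitted within the planned multiple imputation, reporting the adjusted mean difference and 95% CI.

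Site belongs in the model because randomisation is blocked by site. Label the unadjusted t-test or rank test as supportive; a rank test does not in any case yield the mean difference with 95% CI that the section promises. Analyse continuous secondary outcomes in the same way, each on its own baseline.

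The cost is wording only. Baseline ESWT is already collected, linear regression is available in the named software, and no additional patients or visits are needed.
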